#### Economic statistical analysis plan: cost per member per month

The hypotheses are that the new model will increase outreach dental care costs, yet reduce total costs compared with no change in the control model. This is evaluated using a difference in differences approach, adjusting for within cluster variance, to measure the reduction in cost per patient per month for pre versus post intervention effects within the intervention group and for control versus intervention effects. Individual cost components are also evaluated as outcomes in order to elucidate the specific areas of cost which contribute to differences in total costs. Patients in the intervention and control groups are matched using a propensity score based on patient demographics (age, gender, and race), primary medical provider, and primary dental provider. Generalized linear models are constructed using the gamma family with a log-link in order to account for highly skewed cost data. The cost outcomes are the dependent variables while an indicator for the presence of the intervention are the primary independent variable.

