#### Data collection

Data on *impact outcomes* will be obtained through a clinical examination of children and a telephone survey of parents/caregivers and children at baseline and after 24 months. A random sample of Medicaid-enrolled ADS-assigned children will be obtained and stratified by county, at baseline and 24 months post-implementation. The sample will include children whose caregivers either consented or did not consent for care. It will also include children who sought care directly from a dental office. For the survey, staff members will be given a list of enrollees to telephone and move down the list in order until the required sample size is reached. Each individual will be called a minimum of five times. For the clinical examination, staff members will be given a list of enrollees, and they will exam the children in the community settings.

Data on *process and cost outcomes* will be obtained through ADS’s health information systems: Medicaid enrollment database, ADS database (ADIN), electronic dental records and payroll ledger. All Medicaid-enrolled ADS-assigned children population will be included in the process and cost evaluation. Enrollment information including patient identifiers, birth date, gender, race/ ethnicity, coverage dates and assigned primary care provider will be obtained from ADS’s enrollment database and linked to State Medicaid claims. Medicaid claims will be accessed to collect emergency department, medical care and prescription services and costs. Data on *structure outcomes* will be obtained through staff online surveys at baseline and after 24 months and continuously through ADS’s health information systems and internal records. Fidelity information will be obtained through staff surveys and internal records.

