## Discussion

In most states, children enrolled in the Medicaid program have low utilization of dental care and a high prevalence of untreated decayed teeth. Barriers to care and per patient treatment costs can be substantially reduced by a population-based approach to dental care and the provision of basic services outside of traditional clinics. Total expenses increase because more children and mothers receive care. This alternative model does not depend on caregivers taking children to dental offices during work time and can achieve substantial savings in capital costs associated with facilities and equipment and personnel. Children at high risk can be identified and intensive evidence-based effective preventive and curative services provided.

To our knowledge, this intervention will be the first large scale, “real world” test of an alternative delivery and payment model that has the potential to reduce dental care and oral health disparities nationally. This delivery model is replicable in the 47 states where dental hygienists are legally able to provide services to low-income children in community settings under indirect dentist supervision (for example, dentist is not physically present but is on call).

The major challenges for PREDICT are obtaining the permission of community organizations and schools to implement the new dental care system, gaining the cooperation of community leaders, educators, principals and teachers, and getting parents to sign-up for the program. Another challenge is providing the screening, risk assessment and risk-based services to children at community settings cost-effectively. Finally, children with dental diseases or other oral health needs that require treatment in dental offices need to receive it in a timely fashion through well-organized pathways.

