The role of financial incentives in the proposed intervention has special importance. Most incentive plans try to influence the behaviors of the dominant providers, in this case, shareholder and employed dentists. However, a careful assessment of the actual intervention indicates that the EPPDHs and administrative staff are the main drivers of program success. This is because only 25 to 30 % of assigned patients will need to be seen by dentists for curative care in the first few years of the program. Moreover, this proportion will decline as the backlog of disease is treated, and new disease is prevented. Developing sensible incentive plans for the nonprofessional staff is not easy, and this will be one of the first studies to address this issue on a large scale in dentistry or medicine. The incentive plan has to take into account the culture of the organization, the interests of the staff in the intervention program, and other factors. For this reason, incentives are mainly positive rather than negative. That is, high performance is rewarded financially, but average or poor performance does not result in substantial reductions to base pay. In the case of below-average performance, emphasis instead is on performance feedback and development of a specific improvement plan.

In summary, we have presented the trial protocol for the PREDICT quality improvement project and discussed the challenges in implementing and evaluating this new dental care delivery and payment systems in a large dental care organization serving Oregon rural counties.

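### The cost analysis names two units (per member, per patient) and a gamma model with no place for zero-cost members; a users-only analysis could show a saving while cost per enrolled member rises.

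*Protocol article*

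**What the plan says.** The unit is named in two ways. The section heading reads "Economic statistical analysis plan: cost per member per month", while the text beneath it plans a difference-in-differences analysis "to measure the reduction in cost per patient per month for pre versus post intervention effects". That section does not define *patient*.

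The population is stated under Data collection: "All Medicaid-enrolled ADS-assigned children population will be included in the process and cost evaluation".

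The model is stated as: "Generalized linear models are constructed using the gamma family with a log-link in order to account for highly skewed cost data". The same section says that the individual cost components are analysed as outcomes too. The Economic outcomes list includes outreach, screening, preventive and restorative treatment, emergency department visits, inpatient stays and prescriptions. Total cost there is the sum of dental, medical and prescription costs.

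The hypothesis is that "the new model will increase outreach dental care costs, yet reduce total costs compared with no change in the control model". The Discussion, writing about a population-based approach to dental care, expects treatment cost per patient to fall and adds: "Total expenses increase because more children and mothers receive care".

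**The concern.** PREDICT is built to raise the share of enrolled members who receive a dental service, and utilization is a primary process outcome in Table 1. When the number of users changes, cost per user and cost per enrolled member answer different questions and can move in opposite directions.

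The plan leaves two routes to a users-only result. One is to take *patient* as a person who received a service. The other is to fit a gamma likelihood, find that it cannot take zeros, and drop the members who have none of the cost in question. Either route conditions on service use, which the intervention itself changes, so the comparison is no longer between the randomized populations.

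Two things hang on this. Incremental total cost is the numerator of the cost-effectiveness ratio. The Discussion also says that the dental care organization intends to make PREDICT its main delivery model for Medicaid children and mothers if it proves cost-effective.

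**Working it through.** The protocol gives no mean, variance, effect size or power for cost, so there is no figure to reproduce. The check asks whether the choice of denominator can change the sign, and under what conditions.

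**Inputs.** The Sample size section gives detectable utilization increases of about 10 points at rates of 5–10%, 15 points at 20–30%, and 20 points at 40–50%. I use these only as scenarios, starting from 10%, 25% and 45%. Assumptions of mine, not in the protocol:
- an existing user costs c0 = 100 (an index);
- a new user costs r × 100, with r from 0.25 to 1.25;
- existing users' costs do not change;
- nothing changes in the control counties.

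**Formulas.** With utilization u0 before and u1 = u0 + d after:
- cost per member before = u0 × 100; after = u0 × 100 + d × r × 100
- cost per user before = 100; after = (u0 × 100 + d × r × 100) / u1

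**Worked case.** For u0 = 0.45, d = 0.20, r = 0.5:
- per member: 45 before; 45 + 0.20 × 50 = 55 after; 55/45 = 1.222, a rise of 22.2%
- per user: 100 before; 55/0.65 = 84.6 after, a fall of 15.4%

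**All scenarios** (change per user / change per member):

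| Utilization | r = 0.25 | r = 0.5 | r = 0.75 | r = 1 | r = 1.25 |
|---|---|---|---|---|---|
| 10% to 20% | −37.5% / +25% | −25% / +50% | −12.5% / +75% | 0 / +100% | +12.5% / +125% |
| 25% to 40% | −28.1% / +15% | −18.8% / +30% | −9.4% / +45% | 0 / +60% | +9.4% / +75% |
| 45% to 65% | −23.1% / +11.1% | −15.4% / +22.2% | −7.7% / +33.3% | 0 / +44.4% | +7.7% / +55.6% |

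The two measures disagree in sign only when r is below 1.

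**Break-even, free of cost assumptions.** If cost per user falls by a fraction f, cost per member changes by the factor (u1/u0)(1 − f). This exceeds 1 whenever f < 1 − u0/u1. The limits are 1 − 10/20 = 50%, 1 − 25/40 = 37.5% and 1 − 45/65 = 30.8%. A smaller per-user fall is an increase per member.

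**The model.** I use simulated data for 200,000 members in two equal groups, with utilization 45% and 65% and r = 0.5. Users' costs are drawn from a gamma distribution with mean 100 (existing users) or 50 (new users); non-users cost zero. A gamma log-link model was fitted twice:
- users only: cost ratio 0.84 (arithmetic expectation 0.846), an apparent saving
- all members, zeros kept: cost ratio 1.21 (expectation 1.222), equal to the raw ratio of means, an increase

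So the reversal comes from excluding zero-cost members. When zeros are kept, the fitting equations for the mean still return the ratio of means, although a gamma likelihood is not defined at zero.

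**The case against.** The strongest reply is that the plan never says it will analyse users only. The heading says member, and Data collection includes the whole enrolled, assigned child population. The Discussion speaks of assigned patients. The cost-effectiveness section refers to the proportion of patients with untreated caries, which Table 1 defines over all enrolled, assigned children. The matching variables include demographics and primary providers, and Data collection takes demographics and the assigned primary care provider from enrollment data, so matching need not depend on service use. On this evidence *patient* more probably means enrolled member. That stands: a reader might infer from the text that a users-only analysis is fixed, and the documents do not support it.

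It can also be said that handling of zeros is detail for a full analysis plan. That is fair for a missing rule. But the article does commit to a distribution, and that distribution excludes a value that members of the stated population can be expected to take for some listed components.

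The conflict over total cost is only partial. The hypothesis concerns a total that includes medical and prescription costs. The Discussion sentence stands in a paragraph on dental delivery. Dental spending could rise while the wider total falls, and the cost-effectiveness section itself allows for slightly higher total costs. What remains is that the two statements do not say which total they mean.

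A reader might also infer that the early treatment backlog adds to a false saving, because the Discussion expects that "this proportion will decline as the backlog of disease is treated, and new disease is prevented". The inference runs the wrong way. Heavier curative need early on raises early cost. If new users cost as much as existing ones or more (r of 1 or above), the per-user analysis shows no saving.

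**Conclusion.** The point holds in a limited form. The unit is stated inconsistently, and the named model does not fit the population the protocol puts into the cost evaluation. A false saving is possible, not established. It needs a users-only denominator, reached by reading *patient* as service user or by dropping zero-cost members, and it needs new users to be cheaper on average than existing ones.

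Under those conditions, and with relative costs of 0.25 to 0.75, per-user cost falls by about 8% to 38% while per-member cost rises by 11% to 75%. These sizes rest on assumed costs, and on utilization changes that the protocol gives as detectable differences rather than targets. They describe dental cost. For total cost the effect would be smaller, because members with no dental cost may still have medical or prescription cost.

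The gamma family does not itself produce the false saving, since keeping the zeros gives the correct ratio of means. Cost is a secondary objective and the primary caries outcome is untouched, so this is a worthwhile correction to the economic analysis and not a threat to the trial's main result.

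**What to change.** 1. Define every cost outcome, total and component, as cost per enrolled member-month, with the same definition in test and control counties. Replace *patient* with that definition throughout the economic sections.
2. State that members with zero cost stay in the analysis, including in the propensity matching.
3. Replace the plain gamma model with a method that admits zeros: a two-part model whose parts are recombined into a mean per member-month, or a log-link quasi-likelihood or Tweedie model, with variance estimated at county level.
4. Say which cost total is meant in the hypothesis that PREDICT will "yet reduce total costs compared with no change in the control model" and which is meant by total expenses in the Discussion, so that the two can be read together.

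The cost is some rewording and a little extra analysis on data the plan already collects. The real downside is that a saving reported on the looser definition may shrink or change sign.

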##### Selection of participants

The study population is approximately 82,000 children and pregnant women enrolled in Medicaid and living in the 14 counties. The inclusion criteria are as follows:Children younger than 21 years of age and women who are pregnant or up to 2 months postpartum.Enrollment in Medicaid and assigned to receive dental care from ADS.Home address is located in the selected counties.

The age distribution of the children is as follows: 0 to 5 years old, 36 %; 6 to 15 years old, 46 %; and 16 to 20 years old, 17 %. Twenty-one percent of the children and 11 % of the pregnant women are Hispanic, 5 % of children and 4 % of the pregnant women are from other minority races/ethnicities. All pregnant women, new mothers and children <21 years old are enrolled in Medicaid and the Children’s Health Insurance Program.

Recruitment: Participants are identified through a search of the ADS enrollment database. A random subsample of participants is recruited by telephone to participate in an evaluation of the services by completing a telephone survey. Passive informed consent for caries detection and risk assessment at community settings are obtained, as well as active informed consent for treatments provided at these settings.

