#### Randomization and blinding

Each County is considered a single cluster. Clusters are randomized with equal probability to the test or control interventions, using computer-generated random numbers. The allocation schedule for random assignment is generated at the University of Washington by the project biostatistician. The treatment allocation for each cluster is kept in Seattle, and the biostatistician informs local investigators about the treatment allocation, when they are ready to conduct the environmental scan of the test sites. Interviewers are blinded to group allocation. Because of the type of the intervention, personnel involved in the delivery of the intervention and participants are not blinded to group allocation.

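### The cost analysis matches patients on primary medical and dental provider although arms are whole counties; if provider identity is meant, the score largely reproduces the allocation and few patients may have an acceptable match

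*Protocol article*

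**What the plan says.** **How arm is fixed.** Under Randomization and blinding: "Each County is considered a single cluster", and "Clusters are randomized with equal probability to the test or control interventions". There are seven test and seven control counties. Under Selection of participants, a member qualifies by residence: "Home address is located in the selected counties".

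**How cost is compared.** The section headed Economic statistical analysis plan: cost per member per month sets out a difference-in-differences comparison that allows for within-cluster variance. Test and control patients are to be "matched using a propensity score based on patient demographics (age, gender, and race), primary medical provider, and primary dental provider". The model is then specified: "Generalized linear models are constructed using the gamma family with a log-link in order to account for highly skewed cost data".

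**What the provider variable is.** The economic section does not say whether provider means identity or type. The Data collection section lists the enrollment fields to be extracted, including "coverage dates and assigned primary care provider will be obtained from" the organization's enrollment database. That is a record of which provider each enrollee is assigned to.

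**Whose data are used.** The same section states: "All Medicaid-enrolled ADS-assigned children population will be included in the process and cost evaluation".

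**The concern.** Matching on a propensity score works only where the two arms overlap on it. Age, gender and race will overlap well between seven test and seven control counties. Provider will not, if the variable is the named practice or clinician: a practice draws mostly on its own county, and the county is the arm. A score containing provider identity then tends towards one for test residents and zero for control residents.

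This has two consequences. With a caliper, most patients may be discarded, and those kept are an unusual group who live on one side of an arm boundary and use a provider on the other. They are also the group in which contamination between arms is most likely. Without a caliper, everyone is paired, but to someone whose score is far away, so the matching does nothing useful.

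Cost is a stated secondary objective, and incremental total cost is the numerator of the cost-effectiveness ratio. The Discussion says the organization will make the new model its primary one if it proves cost-effective.

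**Working it through.** The article states no matched share, caliper or sample size for the cost analysis, so there is no figure to reproduce. The check asks how much overlap remains.

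**Inputs from the article:** 14 counties, seven per arm; arm set by home county; score covariates age, gender, race, primary medical provider and primary dental provider; age mix 36%, 46% and 17% (47% used for the middle group, so that the shares sum to 100%); 21% of children Hispanic.

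**Assumed, not in the article:** *f*, the share of patients whose provider is in an opposite-arm county (drawn separately for dental and medical); 10 dental and 10 medical providers per county; 20,000 patients; a caliper of 0.2 SD of the logit; 1:1 matching without replacement.

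**Step 1, by hand with one provider variable and equal arms.** A provider in a test county has a true score of 1 − *f*; one in a control county has *f*.
- At score 1 − *f* there are 1 − *f* of the test patients and *f* of the controls, so *f* can be paired.
- At score *f* the shares are reversed, so another *f* can be paired.
- Matchable share = 2*f*, for *f* up to 0.5.

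**Step 2, two independent provider variables.**
- Both providers in test counties: (1 − *f*)² of test and *f*² of control patients, so *f*² can be paired. The same holds when both are in control counties.
- One provider on each side: 2*f*(1 − *f*) of each arm, all of whom can be paired.
- Total = 2*f*² + 2*f*(1 − *f*) = 2*f*, as before.

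**Step 3, simulation with an estimated score** (lightly penalized logistic model with provider indicators):

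| *f* | AUC of score for arm | Matched, simulated | 2*f* |
|---|---|---|---|
| 0 | 1.00 | 0% | 0% |
| 1% | 1.00 | 0.8% | 2% |
| 2% | 1.00 | 2.6% | 4% |
| 5% | 0.995 | 9.3% | 10% |
| 10% | 0.98 | 20% | 20% |
| 20% | 0.91 | 40% | 40% |
| 30% | 0.81 | 60% | 60% |

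The simulation agrees with 2*f* from about 5% upward and falls below it at 1% and 2%.

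**Step 4, who is matched.** In Step 2, matched test patients with at least one opposite-arm provider make up [2*f*(1 − *f*) + *f*²] / 2*f* = 1 − *f*/2 of all matched test patients. That is 97.5% at *f* = 5% and 85% at *f* = 30%. If a patient's dental and medical providers always lie on the same side, Step 1 applies and the share is *f*/2*f* = one half. In either case every pair contains at least one patient with a provider across the boundary.

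**Step 5, no caliper.** In Step 1 with *f* = 5%, the remaining 1 − 0.10 = 90% of pairs would join a score of 0.95 to a score of 0.05.

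**Step 6, provider type instead of identity.** With two type indicators whose mix varies by county (also assumed), the AUC is about 0.54 and about 95% of patients are matched.

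**The case against.** The strongest reply is that the economic section never says identity. If it means the kind of provider, overlap is good and the problem largely disappears. The enrollment field shows what is recorded, not how it enters the score. This stands as a limit on the claim, but identity remains the more natural reading: the text names the provider, not a class of provider, and the field extracted is the assigned provider.

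A reader might infer that nearly all patients are unmatchable. The article does not support that as fact. A loss above 90% needs identity in the score and opposite-arm use of about 5% or less, and neither is given.

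A reader might also see a contradiction with the statement that the whole assigned population enters the cost evaluation. That sentence describes whose data are collected. Drawing matched sets from a full population is not strictly inconsistent with it, and no exclusion of unmatched patients is stated.

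Two further criticisms of the same paragraph are tempting but weak.
- *Zero costs.* The gamma density excludes zero, but the log-link estimating equation, Σ*x*(*y* − *μ*)/*μ* = 0, is defined at *y* = 0. A gamma log-link fit to test data with 90% zeros converged and returned the ratio of arm means exactly.
- *Denominator.* The heading says per member, while the text aims "to measure the reduction in cost per patient per month". The Discussion, however, uses the word patients for assigned members, most of whom are not expected to need a dentist, so this reads as loose usage rather than a different denominator.

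Finally, with only 14 clusters some covariate adjustment is reasonable, and the plan already has difference-in-differences with allowance for clustering. That supports adjusting for demographics. It does not support putting a near-copy of the allocation into the score.

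**Conclusion.** The concern holds in a conditional form. Naming primary medical and primary dental provider as score covariates is a choice the article makes, not detail left to a later document, and on its natural reading it works against the county randomization. If identity is meant, the share acceptably matched is roughly twice the opposite-arm provider share: about 1%, 9%, 20% and 60% at assumed shares of 1%, 5%, 10% and 30%. If type is meant, it is about 95%. These figures rest on the assumed provider counts, caliper and values of *f*.

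The effect is confined to the secondary cost analysis. It reaches the cost-effectiveness ratio only if the ratio uses the matched sample, which the Cost-effectiveness section does not say. A reader might conclude that the ratio is therefore unsound; the text does not go that far. The primary caries analysis uses no matching and is unaffected.

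**What to change.** Preferred: drop the matching. Analyse all enrolled members, the population named under Data collection, by randomized county. Use the planned difference-in-differences with an arm-by-period term, county-level inference, and regression adjustment for age, gender and race/ethnicity.

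Minimum: if matching is kept, remove primary medical and primary dental provider from the score.

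As minor clarifications, state that members with zero cost stay in the model (for example, log-link quasi-likelihood with robust variance) and that the denominator is enrolled member-months.

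The cost is a change of analysis wording. No new data are needed, and the preferred version is less work than matching.
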